### Variables

FPs will provide their data before the start of the study. Patient data will be collected by the recruiting FP, who will also be responsible for patient follow-up. All information will be recorded in a case report form designed for the study. Each FP will access the form from his/her personal computer via the project website using a personal identification code. Three visits are defined for patient data collection: baseline (T0), 6 months (T1), and 12 months (T2) (see Table 1).

**Table 1 Tab1:** Visit plan

	T0 (baseline)		T1 (6 months)	T2 (12 months)	Responsible entity
Confirm inclusion/exclusion criteria	X				FP
Written informed consent	X				FP
Socio-demographic variables	X				FP
Morbidity variables and drug treatment plan	X		X	X	FP
Randomization of FPs		X			RU
FP intervention (intervention group)		X			RT
Patient intervention (intervention group)		X	X		FP
Use of health services	X		X	X	RT
Medication adherence	X		X	X	FP
Medication safety			X	X	FP
Quality of life	X		X	X	FP
Costs				X	RT
MAI	X		X	X	EE EC

*FP* family physician, *RU* research unit, *RT* research team, *EE* external evaluator, *EC* evaluation committee, *MAI* medication appropriateness index

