### Explanatory and adjustment variables

#### Patient (first level) variables

Socio-demographics: age, sex, nationality, AC of residence, marital status, socioeconomic status (monthly salary expressed as multiples of the minimum wage), family composition (number of people living at home), housing indicators, social support (Dukes-UNC-11 questionnaire adapted to Spanish [43]), profession, and social class [44].Morbidity: number and description of chronic diseases based on the International Classification of Diseases in PC (ICPC).Pharmacotherapeutic treatment plan: number and type of drugs prescribed, active ingredient, and dose of each drug.

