#### FP (second level) variables

Socio-demographics: age, sex.Professional performance: years of professional experience, tutor of residents (yes/no), average workload measured as the average number of daily consultations per FP during the year previous to the start of the study.Prior training: in polypharmacy, multimorbidity, and/or shared decision making.

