### Statistical analysis

All analyses will be carried out in accordance with the intention-to-treat principle, with significance set at *p* < 0.05.

Description of baseline characteristics (qualitative and quantitative variables) of patients and professionals for each arm of the study, with corresponding 95% confidence interval (95% CI). Description of patients that abandon the study, including patient characteristics and reasons for loss during follow-up.

Basal comparison between groups using statistical tests for independent samples (Student’s *t* test or chi-square test). Tests for related samples (ANOVA for repeated measures) will be used to analyse changes within groups and between visits.

Analysis of main effectiveness: between-group difference in T1-T0 MAI score, with corresponding 95% CI. Multilevel analysis will be used to adjust models. Difference in MAI score will be considered the dependent variable; baseline patient (first level) and FP (second level) variables and treatment arm will be considered fixed-effect independent variables; and grouping by FP will be considered a random factor. Missing data pertaining to professionals and/or patients will be addressed by replacing missing values with the most recent available or baseline data.

Analysis of secondary effectiveness (non-confirmatory): between-group difference in means or proportions of T2-T0 MAI score will be determined using the appropriate statistical tests and an explanatory model will be adjusted using the same methodology applied to the main outcome variable.

Estimated quality-adjusted life years (QALYs) gained at the population level, with corresponding 95% CI, as determined using parametric methods and bootstrap techniques. Given the 1-year time horizon, no discount rates will be applied.

Calculation of cost-utility ratio: this is an exploratory objective for which a specific design has not been applied. The cost-utility ratio will be estimated by dividing the total cost by the sum of the potential gains expressed in QALYs. A multivariate sensitivity analysis will be performed in which costs will oscillate within the range of uncertainty of a normal distribution. The benefits (QALYs) will also oscillate within the same range.

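### The primary model analyses MAI change but does not name baseline MAI as a covariate, so it gives up precision that data already collected could supply

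*Protocol article*

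**What the plan says.** The Statistical analysis section defines the primary comparison as follows: "Analysis of main effectiveness: between-group difference in T1-T0 MAI score, with corresponding 95% CI". For the multilevel model it adds: "Difference in MAI score will be considered the dependent variable; baseline patient (first level) and FP (second level) variables". These and treatment arm are the fixed effects, and "grouping by FP will be considered a random factor".

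The section on explanatory and adjustment variables uses the same first-level and second-level labels and lists what each contains.

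- Patient level, first group: "Socio-demographics: age, sex, nationality, AC of residence, marital status, socioeconomic status", followed by family composition, housing, social support, profession and social class.
- Patient level, second group: "Morbidity: number and description of chronic diseases".
- Patient level, third group: "Pharmacotherapeutic treatment plan: number and type of drugs prescribed, active ingredient, and dose of each drug".
- FP level: age and sex, prior training, and "Professional performance: years of professional experience, tutor of residents (yes/no), average workload".

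Baseline MAI appears in neither list and is not named as a covariate elsewhere. It is available, because Table 1 schedules the MAI rating at T0, T1 and T2.

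The Randomization section equalises only the number of FPs in each arm. It describes no balancing on MAI.

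**The concern.** Subtracting the baseline is not the same as adjusting for it. A change score fixes the slope of follow-up on baseline at 1. If MAI has equal SDs at T0 and T1 and correlation rho, the actual slope is rho, which is below 1. An arm that starts higher by chance therefore tends to fall more whatever the treatment does, and the change score credits that fall to the arm.

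Randomization removes this on average but not in a single trial, and here only 40 FPs are randomized to each arm. The protocol plans significance tests of baseline differences, but the stated model has no term that would absorb a difference in baseline MAI.

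What is at stake is the width of the primary confidence interval and how far the estimate depends on a chance imbalance that is observed and could be adjusted for. The T2 MAI model is affected in the same way, because the protocol gives it the primary outcome's modelling approach.

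**Working it through.** **Inputs from the protocol (Sample size section):** target difference in MAI change 2; SD of the change 6; power 80%; 5 patients per FP; intraclass correlation 0.03; losses 20%. Significance is set at 0.05 in the Statistical analysis section. The sidedness is not stated, but two-sided reproduces the sample size.

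**Assumed, not in the protocol:** the T0–T1 correlation rho (range 0.3 to 0.9), equal SDs at T0 and T1, and a design effect of 1.12 that is unchanged by adjustment and also applies to baseline MAI.

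**Step 1: reproduce the plan's figure.** The t-based calculation for a difference of 2 and SD 6 gives 142.2 per arm, rounded up to 143, so 286 in total. The design effect is 1 + (5 − 1) × 0.03 = 1.12. Then 286 × 1.12 = 320.3, and 320 / 0.8 = 400. The stated 286, 320 and 400 all reproduce.

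**Step 2: precision of the change score as planned.** With 160 analysed per arm, SE = 6 × √(2 × 1.12 / 160) = 0.710, so the variance is 0.504. Power for a difference of 2 is 80.4%.

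**Step 3: effect of adding baseline MAI.** If the common SD is s, the change-score variance is 2s²(1 − rho). The residual variance after adjusting for baseline is s²(1 − rho²). The ratio is (1 + rho)/2. The change SD is held at the protocol's 6.

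| Assumed rho | Variance ratio | Residual SD | Power at 320 analysed |
|---|---|---|---|
| change score, no adjustment | 1 | 6.00 | 80.4% |
| 0.3 | 0.65 | 4.84 | 93.8% |
| 0.5 | 0.75 | 5.20 | 90.2% |
| 0.7 | 0.85 | 5.53 | 86.3% |
| 0.9 | 0.95 | 5.85 | 82.4% |

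**Step 4: the same loss seen as dependence on imbalance.** Each unit of chance baseline difference moves the change-score contrast by (1 − rho) units. At rho 0.5 the implied SD of baseline MAI is 6 / √(2 × 0.5) = 6, so one SE of baseline imbalance is 0.710. The resulting shift is 0.5 × 0.710 = 0.355.

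This is not an addition to Step 3. The adjusted variance is 0.75 × 0.504 = 0.378, the gap is 0.504 − 0.378 = 0.126, and 0.355² = 0.126. The shift and the variance loss are one quantity expressed in two ways.

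**Step 5: choice of outcome.** Change is T1 minus T0. Once T0 is a fixed effect, replacing T1 by change lowers the coefficient of T0 by 1 and leaves the arm coefficient as it was. The treatment effect is the same either way.

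**The case against.** **Nothing in the plan is invalid.** The objective, the sample size and the analysis all use MAI change, the sample size reproduces, and the change-score contrast is unbiased over randomizations. All of this stands. A reader might infer that the primary result is biased by regression to the mean, or that the trial is underpowered. The protocol supports neither. The dependence on baseline imbalance is already reflected in the SE of the change score, and the planned power is met under the protocol's own inputs.

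**The omission is inferred.** The phrase on baseline patient variables could loosely cover MAI, the lists are not called exhaustive, and exact covariates are often left to the SAP. This stands in part. Against it, the article goes beyond announcing an adjusted model: it names the outcome and the covariate levels, and it defines those levels under the same labels without MAI. A reader following the text would leave MAI out.

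**The comparator is too weak.** The planned model already adjusts for number and type of drugs and for morbidity, which may recover part of the gain. This stands, and it makes the figures in the table upper values.

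**Further criticisms of the covariate list.** A reader might also infer that patients with missing covariates would be dropped. The Statistical analysis section instead plans to replace missing values and nowhere plans complete-case deletion. A reader might want the other covariates moved to a secondary analysis. That is a preference, and the Discussion gives a reason for adjusting for FPs' prior training in the multilevel model.

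**Conclusion.** The point holds as one of efficiency and conditional accuracy. As written, the primary model lacks the outcome's own baseline value, which the trial collects. The analysis remains valid and has about 80% power.

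Adding baseline MAI would cut residual variance by 35% at rho 0.3, 25% at 0.5, 15% at 0.7 and 5% at 0.9. Power at 320 analysed would rise from 80.4% to between 93.8% and 82.4% over that range. The gain is material at low to moderate correlation and small near 0.9.

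These figures rest on the assumed rho, equal SDs and an unchanged design effect, and on comparison with a change score that has no other covariates. They are therefore ceilings on the gain over the model actually planned.

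**What to change.** In the Statistical analysis section, and in the SAP if it does not already do so, name baseline MAI as a fixed-effect covariate in the primary multilevel model, alongside treatment arm and the listed patient and FP variables, with the random effect for FP kept. Either T1 MAI or the change may be the outcome.

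The T2 MAI model takes up the same covariate through the protocol's existing cross-reference to the primary method, so it needs no separate wording. The sample size and the estimated quantity do not change. The cost is one sentence and no new data, and it should be settled before the outcome data are analysed.

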### Sample size

The sample size was calculated under the hypothesis that the intervention would lead to a difference of at least 2 units in the change in MAI score at 6 months (T1 vs T0) (i.e. a clinically relevant difference) between study groups. Differences in MAI are assumed to be normally distributed in each intervention arm and the variances are assumed to be equal. According to previous studies, the standard deviation of the difference in MAI is 6 units [32–34]. Therefore, the study should be capable of detecting an effect size of 0.3 (2/6). Considering a power of 80% and assuming simple random sampling, the required sample size would be 286 patients (143 patients in the intervention group and 143 in the control group).

The effective sample size in this type of study design depends on the average size of the cluster and the degree of correlation between individuals in the cluster. Accordingly, it is necessary to adjust the calculated sample size in accordance with the design effect (DE). An average cluster size of 5 patients per FP and an intraclass correlation coefficient of 0.03 [35] produces the following (DE = 1 + (5 − 1) × 0.03 = 1.12) which gives a sample size, corrected for the DE, of 320 patients. Assuming a percentage of losses of 20%, the final sample size required is 400 patients (200 per group). Assuming that each FP will recruit 5 patients, 80 FPs (40 per group) will be required. In each AC, 133 patients will be recruited.

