### Randomization

The unit of randomization is the FP and the unit of analysis the patient. Randomization of the FP will be achieved using the treatment assignment module of the Epidat 4.1 program; the proposed intervention will be considered the treatment and usual care considered the control. To ensure an equal number of FPs in each group (intervention and control), the ‘balanced groups’ option will be selected.

Once all participating FPs have selected their patients and collected the corresponding baseline data, FP randomization will be performed centrally by the Unidad de Apoyo a la Investigación, Gerencia Asistencial de Atención Primaria in Madrid. Subsequently, each FP will receive the information on the study group to which they have been assigned, at which point all patients recruited by him or her will be included in that group.

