#### Secondary outcomes

Use of health services: unplanned and/or avoidable hospitalizations, use of emergency services and PC (FP and nurse).Quality of life: measured using the EuroQol 5D-5L questionnaire [38, 39].Medication safety: measured as the incidence of adverse drug reactions and potentially hazardous interactions, classified using the taxonomy proposed by Otero-López [40].Treatment adherence: measured using the Morisky-Green test [41] and the Haynes-Sackett questionnaire [42].Patient perception of shared decision making: measured using a single, multiple choice question, formulated ad hoc.Cost-utility: time spent on training FPs, cost of teaching staff, time spent on physician-patient interviews, utilities measured using the EuroQol 5D-5L.

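### The general carry-forward rule, if applied as worded to medication safety and service use, yields either no value or one from the wrong period

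*Protocol article*

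**What the plan says.** All references are to the protocol article.

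- **Statistical analysis.** The only missing-data rule reads: "Missing data pertaining to professionals and/or patients will be addressed by replacing missing values with the most recent available or baseline data". It is the last sentence of the paragraph on the primary MAI comparison and its multilevel model. The same section commits all analyses to intention-to-treat.
- **Secondary outcomes.** Medication safety is "measured as the incidence of adverse drug reactions and potentially hazardous interactions". Use of health services covers hospitalisations, emergency care and primary care contacts.
- **Variables, Table 1.** The safety row is "Medication safety X X FP": the two marks fall under T1 and T2, and the T0 cell is empty. The service-use row is "Use of health services X X X RT": T0, T1 and T2, with the research team responsible rather than the family physician (FP).
- **Randomization.** "Once all participating FPs have selected their patients and collected the corresponding baseline data, FP randomization will be performed centrally". Every T0 value therefore precedes allocation.
- **Sample size.** The size for the 6-month change in MAI is raised to allow for 20% losses.

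**The concern.** A MAI score describes the state of a prescription list and has a T0 value, so carrying it forward at least produces a quantity of the right kind, whatever else may be said about the method. An incidence of adverse drug reactions or a number of admissions is accumulated over a period. Replacing it with an earlier value gives nothing if no earlier period was recorded, and otherwise gives the count of a different period.

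At stake are two named secondary outcomes. For safety, some patients would have no value under the rule, and the article does not say what then happens to them despite its intention-to-treat statement. For service use, some follow-up values would be counts that the intervention could not have influenced.

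**Working it through.** **Step 1. The plan's own figure.** Difference 2, SD 6, 80% power, two-sided 5%: the t-based solution is 142.2, so 143 per arm and 286 in total. Design effect 1 + (5 − 1) × 0.03 = 1.12; 286 × 1.12 = 320.3, stated as 320. With 20% losses, 320 / 0.80 = 400. The stated size reproduces, and nothing below alters it. The loss allowance is 0.20 × 400 = 80 patients (40 per arm), set for MAI at 6 months. The article does not say what share of safety or service-use data would be missing.

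**Step 2. What the rule returns, from Table 1 and the rule side by side.**

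| Outcome | Lost before T1 | Seen at T1, lost before T2 |
|---|---|---|
| MAI | T0 score | T1 score |
| Medication safety | nothing: no T0 value exists | T1 value |
| Use of health services | T0 count, from before randomisation | T1 count |

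The safety cell for loss before T1 follows from the two places alone and needs no assumption beyond applying the rule to this outcome. If safety events are recorded per interval, which is not stated, the T1 value placed at T2 would count the same reactions twice. Repeating the T1 service-use count has the same weakness under the same condition.

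**Step 3. Illustration for service use.** Assumptions, none given in the article: a share f of follow-up counts is replaced by T0 counts, f is equal in both arms, and the T0 rate and look-back match usual-care follow-up (scaled to 1). Then

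estimated ratio = (1 − f) × RR + f × 1.

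| True RR | f = 0.10 | f = 0.20 |
|---|---|---|
| 0.80 | 0.82 | 0.84 |
| 0.70 | 0.73 | 0.76 |
| 0.50 | 0.55 | 0.60 |

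For RR 0.70 and f = 0.20, the share of the log effect lost is 1 − ln(0.76)/ln(0.70) = 1 − 0.274/0.357 = 0.23.

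**Step 4. Sensitivity to the look-back, which is not stated.** If T0 covered 12 months against a 6-month follow-up interval, the carried count would be 2 rather than 1 in both arms. For RR 0.80: at f = 0.10, (0.9 × 0.80 + 0.1 × 2)/(0.9 + 0.1 × 2) = 0.92/1.10 = 0.84; at f = 0.20, (0.8 × 0.80 + 0.2 × 2)/(0.8 + 0.2 × 2) = 1.04/1.20 = 0.87.

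**Step 5. Safety.** No bias figure is computed. The rule gives no value for patients lost before T1, and the article does not say how they would then be handled.

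**The case against.** The strongest reply is about scope. The sentence ends the MAI paragraph, and its mention of professionals and patients echoes the two levels of the model just described. The secondary-analysis paragraph that follows names only the T2-T0 MAI score. No model or denominator is given for safety or service use, and an article may leave those to a full plan that is not shown. This stands in part: the rule's reach to event outcomes is inferred from its general wording. But the point is not that detail is missing. The one rule that is printed carries no limit and does not fit two listed outcomes. If it was meant for MAI only, the text should say so.

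Four stronger readings are tempting and are not supported:

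- *Event outcomes cannot be scored at all.* This is literal only for safety in patients lost before T1. Service use does receive a value, though from the wrong period.
- *The plan puts 80 patients on this path for service use.* The 20% comes from the MAI sample size. The research team collects service use from an unstated source, so a missed FP visit need not mean a missing count.
- *Losses would be counted as event-free, giving a false safety difference.* Nothing in the article says so, and the rule does not produce it.
- *Every component is a transient event, and every effect is pulled towards no difference.* Hazardous interactions can persist as long as the prescriptions do. The dilution in Step 3 depends on equal losses and a matching baseline rate and look-back.

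It is also fair to say that analysing observed time does not rescue a patient with no follow-up contact, and so departs from full intention-to-treat itself. That stands and is stated as a cost below.

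**Conclusion.** The point holds in a limited form. Applied as worded, the carry-forward rule gives no medication-safety value for patients lost before T1, and gives a pre-randomisation count as the follow-up service use of patients without later data. Repetition of T1 events at T2 is a further problem only if recording is per interval.

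The effect on service use is illustrative: 0.70 estimated as about 0.76 at 20% missing and 0.73 at 10%, under the assumptions in Step 3. The true share missing could be smaller.

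Severity is minor to moderate. The outcomes are secondary, and the article labels secondary effectiveness as non-confirmatory. The primary MAI analysis and the sample size of 400 are untouched by this point.

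**What to change.** 1. State that carry-forward does not apply to medication safety or to use of health services.
2. Analyse both over observed time after randomisation, for example with a Poisson or negative binomial model with log observed time as offset and a random effect for FP. For service use, enter the T0 count as a covariate.
3. Obtain service-use data for patients who miss visits wherever the research team's source allows.
4. Report by arm the number of patients with no post-randomisation data for each outcome, and add a simple sensitivity analysis for them.

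**Cost.** A few sentences of analysis wording, an end-of-observation date for each patient (Table 1 does not list one), and some effort to retrieve service-use records. No extra visits or patients are needed. Patients with no post-randomisation data do not contribute to the main analysis of these outcomes, which assumes that losses are unrelated to later events given the covariates. The sensitivity analysis is there to show how far the result depends on that assumption.

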FPs who agree to participate in an experimental study are potentially more interested in the subject, just as patients who agree to participate may share certain common features in terms of health-related awareness and motivation, which can lead to bias. Although better results than those obtained including less selective participants may occur, this phenomenon would have a conservative effect (i.e. it would decrease the magnitude of the difference between the two groups). Moreover, participating FPs could modify or improve their prescribing habits just as a response to their awareness of being observed (Hawthorne effect). This may dilute differences between intervention and control groups regarding the appropriateness of prescription.

Although the analysis of the effect of the intervention on quality of life is non-confirmatory and the expected changes are limited over a short period of time, we consider it essential to include this outcome in the study. Firstly, between-group differences may be detected despite not being highly significant, and secondly, measurement of quality of life changes allows the incorporation of outcome variables reported by patients themselves, and facilitates the calculation of utilities for the cost-utility analysis. This will enable responding to some of the shortcomings and limitations of previous interventions as detected by Patterson et al. [25].

It is essential to provide evidence concerning interventions on PC patients with polypharmacy and multimorbidity, conducted in the context of routine clinical practice, and involving young-old patients with significant potential for preventing negative health outcomes.

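### The carry-forward rule scores every patient without a T1 MAI as zero change, which shrinks the primary estimate and makes its confidence interval unreliable

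*Protocol article*

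**What the plan says.** The missing-data rule stands in the main-effectiveness paragraph of the protocol article's Statistical analysis section: "Missing data pertaining to professionals and/or patients will be addressed by replacing missing values with the most recent available or baseline data". The same paragraph defines the primary result: "Analysis of main effectiveness: between-group difference in T1-T0 MAI score, with corresponding 95% CI". On the multilevel model it adds: "Difference in MAI score will be considered the dependent variable".

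The Variables section fixes when data exist: "Three visits are defined for patient data collection: baseline (T0), 6 months (T1), and 12 months (T2". Table 1 schedules MAI at those three visits and at no other time.

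The Sample size section plans for "a difference of at least 2 units in the change in MAI score at 6 months (T1 vs T0", takes it that "the standard deviation of the difference in MAI is 6 units", and allows for attrition: "Assuming a percentage of losses of 20%, the final sample size required is 400 patients (200 per group".

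The article gives no reason for assuming that lost patients do not change. The only sensitivity analysis it describes is for cost-utility. For losses it otherwise promises a description of the patients lost and their reasons.

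**The concern.** No MAI is taken between T0 and T1. For a patient with no T1 value, the most recent value and the baseline value are therefore the same number. Carrying it forward sets T1 equal to T0 and the change to 0. This follows from the visit plan and needs no assumption about behaviour.

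Zero is a neutral fill-in only if lost patients truly do not change. The trial is sized on the hypothesis that mean change differs by 2 units between arms, so under that hypothesis at least one arm has a non-zero mean change. Mixing imputed zeros into that arm moves the estimate away from the quantity the trial was designed to measure. The analysis model then treats all 400 values as observed. What is at stake is the confirmatory estimate and its 95% CI, which are the stated primary result.

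**Working it through.** **Inputs from the protocol article.** Difference 2, SD of change 6, design effect 1 + (5 − 1) × 0.03 = 1.12, losses 20%, 400 patients (200 per arm), significance 0.05 (taken as two-sided, which reproduces the stated size). **Not given, so assumed:** mean change in each arm, and loss in each arm.

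**The plan's own figure.** The normal approximation gives 2 × (6 × (1.96 + 0.842)/2)² ≈ 141.3, so 142 per arm. The t-test version gives 142.25, so 143 per arm, or 286. Then 286 × 1.12 = 320.3 and 320/0.80 = 400. The stated 286, 320 and 400 reproduce.

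**Effect of the rule.** Let m be the mean improvement and p the proportion without T1 in an arm, with loss unrelated to outcome:

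- expected estimate D = (1 − p_I)·m_I − (1 − p_C)·m_C
- variance per arm v = (1 − p)·36 + p(1 − p)·m²
- SE = √[1.12 × (v_I + v_C)/200]

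**Equal 20% loss, improvements 2 and 0.**

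- D = 0.8 × 2 − 0.8 × 0 = 1.6. With equal loss, D = 0.8 × 2 = 1.6 whatever the arm means.
- v_I = 28.8 + 0.16 × 4 = 29.44 and v_C = 28.8, so SE = √(1.12 × 58.24/200) = 0.571.
- Coverage of the true value 2: the shift is 0.4/0.571 = 0.70 SE, so Φ(1.26) − Φ(−2.66) = 0.892.
- Power: 1.6/0.571 = 2.80, so about 0.80. The zeros shrink the variance as well as the estimate.
- SE from the 160 per arm actually observed: √(1.12 × 72/160) = 0.710.

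**Unequal loss, true difference 2 (assumed means and splits).**

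| Improvement I / C | Loss I / C | Expected estimate | Power |
|---|---|---|---|
| 2 / 0 | 30% / 10% | 1.4 | 0.69 |
| 2 / 0 | 10% / 30% | 1.8 | 0.89 |
| 3 / 1 | 30% / 10% | 1.2 | 0.55 |
| 3 / 1 | 10% / 30% | 2.0 (errors cancel) | 0.94 |
| 4 / 2 | 30% / 10% | 1.0 | 0.40 |
| 4 / 2 | 10% / 30% | 2.2 (overstated) | 0.97 |

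**No true effect, both arms improving by m.** Rejection probability = Φ(|D|/SE − 1.96) + Φ(−|D|/SE − 1.96). The spurious difference favours the arm with less loss.

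| m | Loss, one arm / other | Spurious difference | Type I error |
|---|---|---|---|
| any | equal | 0 | 0.05 |
| 1 | 30% / 10% | 0.2 | 0.064 |
| 2 | 25% / 15% | 0.2 | 0.064 |
| 2 | 30% / 10% | 0.4 | 0.107 |
| 3 | 25% / 15% | 0.3 | 0.081 |
| 3 | 30% / 10% | 0.6 | 0.178 |

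**Without imputed zeros.** If data are missing at random and the analysis is valid under that condition, the expected difference stays at 2.0. With 160 per arm observed, 2/0.710 = 2.82 and power is 0.804, which is what the sample size planned for.

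**The case against.** The best defence is that, with equal loss and a real benefit, the rule pulls the estimate toward the null and leaves power near 0.80, so it cannot manufacture a success. That stands for equal loss. It does not rescue the estimate or the interval, and it fails once loss differs by arm and the arms change on average.

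A second defence is that unequal loss is conjecture. The article gives no arm-specific loss or mean change, and it takes steps to keep FPs in the trial: stable employment as an entry criterion, individual follow-up and incentives, and later training for control FPs. This also stands, so the unequal-loss results are conditional illustrations. They are not fanciful: the intervention is unmasked, only intervention FPs deliver the interviews, and the recruiting FP collects patient data, so one FP who withdraws can take about five patients with them.

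Third, the sentence could be read as covering covariates. It is not limited to them, and it sits in the primary-outcome paragraph.

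Fourth, missing at random is itself untestable. Where an FP leaves before giving the interview, little change may be the more plausible outcome. That supports a sensitivity analysis, not a primary analysis that fixes zero for everyone.

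A reader might also infer three stronger points that the article does not support:

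- **That the rule contradicts the sample size.** Inflating for losses is ordinary planning, the figures reproduce, and power under equal loss is about 0.80.
- **That the plan expects both arms to improve.** The Discussion says only that "participating FPs could modify or improve their prescribing habits just as a response to their awareness of being observed", as a possible limitation.
- **That the rule credits QALYs after death.** It sits in the MAI paragraph, the QALY and cost-utility analyses have their own paragraphs, and nothing says utilities are carried past death.

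**Conclusion.** The point holds for the primary MAI analysis. That a patient without T1 is scored as zero change is certain from the stated rule and visit plan.

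At the planned 20% loss, assumed equal by arm and unrelated to outcome, the estimate is attenuated by a fifth (2 to 1.6) and coverage of the nominal 95% CI is about 89%. The SE of about 0.57 describes the attenuated quantity and is smaller than the 0.71 that the observed patients support. Power is not the casualty.

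The direction of bias under unequal loss is not fixed. With no true effect, type I error runs from about 6% (25/15 loss, both arms improving 2) through about 11% (30/10, improving 2) to about 18% (30/10, improving 3). The last figure is the severe end of that range and should not be read as a forecast. All these figures use an unadjusted comparison with the design effect applied to the variance. An SAP that is not shown might add sensitivity analyses, but the rule for the primary analysis is fixed in this text.

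**What to change.** Remove carry-forward as the primary rule, using one of two replacements:

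- Estimate the T1 contrast from a likelihood-based multilevel model on all observed MAI values (T0, T1, T2), with arm-by-visit terms and random FP and patient effects.
- Keep the change-score multilevel model and apply multiple imputation that respects FP clusters.

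Both are valid under missing at random, and the text should state that assumption. Keep carry-forward only as a labelled sensitivity analysis, and add one for data missing not at random, for example by shifting the imputed changes in lost patients over a stated range, separately by arm.

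The cost is changed wording in the protocol and SAP and modest extra analysis work. No new data, visits or patients are needed, and the sample size can stand.
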